### Measures

Table 4 presents a summary of the measurements utilized in the student questionnaires at each assessment time-point. For a comprehensive overview of the measurements employed in the student, teacher, and interventionist surveys, including construct order, number of items, translated example items, and source references, see Supplementary 2, Tables S2–S5. Most constructs are assessed using brief two- to three-item scales, with a small number of single-item measures to reduce respondent burden for the target group. Key proposed mechanisms are measured using well established operationalizations from the Reasoned Action Approach and related research^51^. A small number of measures were drawn from previous studies (see Supplementary 2) based on their psychometric properties. Other scales assessing mechanisms and covariates were developed within the project. In our feasibility sample, internal consistency for all multi-item scales used in the student questionnaire was acceptable (Cronbach’s α = 0.72–0.83).

**Table 4 Tab4:** Summary of measurements used in the student questionnaires.

Measurement	T0	T1^a^	T2	T3	T4	Tn
*Outcomes*						
Intention to be vape- and smoke-free^b^, susceptibility to vaping and smoking	X	X	X	X	X	X
Lifetime prevalence, 12-month and 30-day prevalence, current vaping/smoking, regular vaping/smoking, 30-day frequency	X		X	X	X	X
*Proposed mechanisms / mediators*						
Personal agency: self-efficacy to be vape- and smoke-free, refusal self-efficacy, refusal self-concept	X	X	X	X	X	X
Action planning	X	X	X	X	X	X
Descriptive and injunctive norms towards being vape- and smoke-free	X	X	X	X	X	X
Attitude towards being vape- and smoke-free (direct measure)	X	X	X	X	X	X
Outcome expectations (indirect attitude measure)	X	X	X	X	X	
Stress and problem coping self-efficacy, stress and problem coping planning, affect^a^, anxiety^a^				XX	X	X
*Program evaluation*						
Satisfaction		X	X	X		
Careful responding /attention	X	X	X	X	X	X
*Sociodemographics and covariates*						
Age, gender	X	X	X	X	X	X
SDOH, country of origin, objective SES, subjective SES, ethnicity/racial identity, language, religion, general health	X					
Vaping/smoking of relevant others, parental disapproval of vaping/smoking, accessibility, school attachment, self-esteem, satisfaction with looks, distress	X					

T0: baseline, conducted approximately one week or immediately before the first core workshop, T1: immediately after core workshops 1 and 2, T2: 3 months post-intervention, after booster session, T3: 6 months post-intervention, after life skills training, T4: 12 months post-intervention (assessment only), Tn = optional follow-up surveys up to the age of 21. “XX” indicates assessments conducted both immediately before and after the workshop in the treatment condition (T3).

^a^ measured only of the intervention arm participants.

^b^ intention will be modelled as an additional mediator of intervention effects on behavioral outcomes, alongside the other proposed mechanisms (e.g., self-efficacy, refusal self-concept, action planning).

Given the linguistic and educational diversity of the study population, these questionnaires were phrased using simplified wording and grammar. Assessors will be trained to develop a shared understanding of questionnaire constructs and item meanings in order to support standardized clarifications during data collection. Recurring clarification needs, particularly during baseline assessments, are discussed in weekly staff meetings and incorporated into the assessment script to further standardize assessor support across schools.

*Primary endpoint (T4).* The primary endpoint for this study is the difference in students’ *intention to be vape- and smoke-free* (i.e., to abstain from using any vaping or tobacco product) between intervention and control groups (primary endpoint measured at T4, 12 months post-intervention). This endpoint will be measured by two items on a 5-Point-Likert-Scale, i. e.: “I want to be smoke-free (that is, not to smoke) for the next six months” (1 = *strongly disagree*, 5 = *fully agree*)^51^).

*Secondary behavioral endpoints.*
*Susceptibility to vaping or smoking*, capturing the absence of a strong commitment not to vape and smoke^82^, will be assessed based on items used in previous research^83,84^ and coded binarily (0 = *Committed non-vapers and non-smokers*, 1 = *Susceptible to vape or smoke*). Students will be asked to report their expected behavior in three scenarios: “Do you think you will try smoking in the future?”, “If one of your closest friends offered you something to smoke, would you smoke it?”, “Do you think you will smoke at some point within the next year?”, using a 4-Point-Likert scale (1 = *definitely not*, 4 = *definitely*). Students will be considered committed non-vapers and non-smokers (vs. susceptible to vaping or smoking) only if they report “definitely not” on all questions. This dichotomization is consistent with the established susceptibility index literature showing strong prospective predictive validity of the binary measure for initiation of cigarette and e-cigarette use^82,85^. Alternative codings, including categorical and continuous versions, will be explored in secondary/sensitivity analyses as specified in the preregistration^37^.

*Lifetime, 12-month, and 30-day prevalence of vaping and smoking* (binary coding), *30-day-frequency, current use* (binary coding; any current consumption, including only occasional use during the last month), and *regular use* (binary coding; vaping or smoking more than once a week during the last month), will be assessed using adjusted measures from the KiGGS (German Health Interview and Examination Survey for Children and Adolescents, Wave 1)^86,87^*.* Prevalence and frequency measures will be collected separately for individual product categories (i.e., cigarettes, disposable e-cigarettes, reusable/refillable e-cigarettes, hookah, tobacco heater, cigars/ cigarillos, pipe) and will be aggregated to calculate prevalence/frequencies across products for the main analysis.

*Proposed mechanisms (mediators).* As specified in our logic model, the main proposed determinants of behavior and mechanisms of change to be underlying the intervention effects on the primary outcome (intention to be vape- and smoke-free) include self-efficacy to be vape- and smoke-free, refusal self-concept, refusal self-efficacy, action planning, descriptive and injunctive norms towards being vape- and smoke-free, and attitudes towards being vape- and smoke-free (direct measure). For behavioral outcomes (i.e., susceptibility, prevalence, and frequency), intention will be modelled as an additional mediator alongside the mentioned psychosocial determinants (e.g., self-efficacy, refusal self-concept, action planning). In addition to the quantitative assessment of mediators via student questionnaires, the proposed mechanisms of change will be explored qualitatively in semi-structured interviews conducted after the core workshop.

*Additional measures.* The baseline assessment will include a number of sociodemographic variables and proposed determinants of vaping and smoking. Among these, age, gender, objective SES, school attachment, parental vaping/smoking, best friend’s vaping/smoking, self-esteem and distress will serve as covariates in the main analysis of intervention effects on the primary outcome. In addition, we will assess SDOH to examine differential intervention efficacy and underlying mechanisms of action by SDOH subgroup. For the purpose of sensitivity analyses, the student questionnaires will also include different attention screeners (e.g., “Please show us that you are reading the questions carefully and mark response option ‘Definitely’; “How much do you agree? ‘I am currently responding to a questionnaire’) and an item to detect careless responding^88^.

*Fidelity, acceptability, reach.* We will examine *reach* using descriptive, quantitative information on rates of school and of student consent and participation in different study waves (see^37^ for a detailed list of indicators). *Fidelity* data will be obtained from teacher (after teaching the teacher booster session at T2) and interventionist self-reports (after teaching at T1, T2, and T3) on the quality of their intervention delivery. Ratings will include measures adapted from previous studies, i.e., the *overall quality* and quality of different parts of the workshops [^70^*]*, as well as the study team’s self-reported *competence in program delivery*^89^ and autonomy-supportive interaction style [^65^]  (e.g., use of appropriate language, adjusting the pace to students’ needs, reflective listening, empathic paraphrasing, building on students’ contributions, and actively engaging students), as well as *dose* (rate of intervention sessions taught as planned; duration of each session; percentage of intended content delivered per part; as well as substantive deviations from the intervention protocol).

*Acceptability* measures are collected from teachers observing the core workshop (T1) as well as from students and interventionists after the core workshop (T1), the study team’s booster session (T2) and the life skills training (T3). These include teacher- and student-reported satisfaction with the program^52^ and positive and negative events reported by teachers and interventionists.

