### Cluster-randomized controlled trial protocol

The primary objective of the trial is to assess the effects of a school-based prevention program with three training sessions on motivation, smoking, and vaping (primary outcome: intention to be vape- and smoke-free across all modes of use) in children in Grade 5 (Age: 10–11 years) at 3, 6, and 12 months after baseline, compared to an active control group receiving the standard curriculum. Smoking and vaping measures include the use of cigarettes, disposable e-cigarettes, reusable e-cigarettes, hookah, tobacco heater, cigars/cigarillos, and pipe.

We will report intervention content based on the well-established Behavior Change Technique Taxonomy^49^ and examine underlying mediators of the program effects. We will recruit students from schools with elevated sociostructural burden and examine risk and protective factors, intervention effects and mechanisms of action in relation to students’ SDOH. The assessment and analysis of both mediating mechanisms and SDOH as moderators are expected to advance a “precision approach” to prevention – bringing us closer to providing the right preventive intervention to the right person at the right time and in the right place^31,57^.

We hypothesize that children in the intervention group, compared with children in the control group, will exhibit

Increased intentions to be vape- and smoke-free (primary endpoint measured at the 12-month follow-up) andDecreased susceptibility to vaping/smoking; vaping/smoking prevalence (lifetime prevalence, 12-month and 30-day prevalence, as well as 30-day-frequency), regular vaping/smoking (≥ once a week), and current vaping/smoking (≥ once a week during the last month).The intervention effects are mediated via 
increased action planning for vaping/smoking refusal; increased vaping/smoking refusal skills (i.e., refusal self-concept and refusal self-efficacy as proxies for actual capabilities); increased self-efficacy to be vape- and smoke-free; increased positive attitudes towards being vape- and smoke-free,increased stress and problem coping (i.e., self-efficacy and planning for coping); and heightened intentions to be vape- and smoke-free (for the outcomes of susceptibility and vaping/smoking behavior only); decreased perceived vaping/smoking norms; decreased negative attitudes towards being vape- and smoke-free.

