### Intervention and comparator

The intervention is taught during school hours by a tandem of research assistants with an expertise in human medicine, health sciences or psychology (i.e., (under-)graduate students or professionals), whose members alternate in leading the intervention (i.e., the psychologist discusses mental health and addiction; the medical practitioner explains biological processes).

The intervention program comprises three basic components that are conducted at three-month intervals in the course of one school year:A 180-min *Core Workshop* delivered by the study team that can be taught in two separate sessions. The primary objective of this workshop is to educate students about the consequences of vaping and smoking, enabling them to identify and resist unfavorable social influences and to cultivate positive social norms. Additionally, the workshop aims to facilitate the acquisition of critical thinking about the influences of advertising and social media.A 90-min mid-term *Booster Session*, which serves to refresh and deepen the content of the core workshop. The booster consists of two parts: approximately 45 min taught by the class teacher and 45 min taught by the study team. The teacher-led part consists primarily of the students creating a poster advertisement for a vape- and smoke-free life, a task that can be implemented with minimal teacher preparation and no additional training. Materials are provided to schools in advance, and the task serves as preparation for the subsequent visit by the study team.A 90-min, more comprehensive *Life Skills Training* module, led by the study team, focusing on problem solving and managing uncomfortable emotions, such as stress and anxiety.

An overview of intervention content, employed BCTs and targeted theoretical determinants is provided in Table 3.

**Table 3 Tab3:** Overview of workshop modules, key content, BCTs and targeted theoretical determinant of vaping and smoking behavior.

Workshop	Content/key message	Key BCTs^a^	Key change objective in our assessment model^a^

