### Analysis

The analyses on intervention effects will be conducted on an intention-to-treat basis, including data from all students based on the groups they were randomly assigned to. The main confirmatory analysis pertains to the group difference between intervention and control group in intention to be vape- and smokefree at the 12-month follow-up (T4), adjusted for baseline (T0). All other analyses, including analyses of secondary behavioral outcomes and additional time points, will be considered secondary or exploratory, and no formal multiplicity adjustment will be applied.

Group differences in secondary behavioral endpoints (i.e., prevalence and frequency measures) will be analyzed across all product categories (e.g., prevalence defined by the use of at least one of the products presented in the questionnaire) as well as individually for each product reported by at least 1% of the sample.

For continuous and dichotomous outcomes, we will use generalized mixed effect regression analyses (i.e., linear regression for the outcome of intention to be vape- and smoke-free; logistic regression for [binary] susceptibility, prevalence measures, current vaping/smoking and regular vaping/smoking). The primary analyses will use a two-level structure, with students at Level 1 nested within schools at Level 2, reflecting the school-level randomization and the role of the school as the primary clustering unit. In regard to count data, we will use Generalized Estimating Equations to conduct zero-inflated negative binomial regressions for count outcomes with many zeros, i.e., the 30-day frequency. We will investigate intervention effects using the criterion of statistical significance (*p* < 0.05) of the regression coefficients for the treatment condition variable (adjusting for prespecified baseline covariates; all measured at T0: intention, age, gender, parental vaping/smoking, best friend’s vaping/smoking, objective socioeconomic status, school attachment, self-esteem and distress). All models will be specified with a maximal random effects structure and progressively simplified as needed to reach convergence.

To handle missing data appropriately, we will conduct a comprehensive analysis of attrition patterns, multiple imputation and sensitivity analyses to check the robustness of our inferences to departures from the underlying assumption of missingness at random.

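### Twelve-month prevalence, read as compared between arms at T2 and T3, looks back about 9 and 6 of its 12 months before baseline, which dilutes those secondary contrasts (minor)

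*Protocol article*

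**What the plan says.** The section that opens the trial protocol (Cluster-randomized controlled trial protocol) sets the objective as effects on motivation, smoking and vaping "at 3, 6, and 12 months after baseline, compared to an active control group receiving the standard curriculum". Its hypotheses include lower "vaping/smoking prevalence (lifetime prevalence, 12-month and 30-day prevalence, as well as 30-day-frequency", without tying any of these to a single wave.

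Table 4 (Measures) lists "Lifetime prevalence, 12-month and 30-day prevalence, current vaping/smoking, regular vaping/smoking, 30-day frequency" in one row, marked at T0, T2, T3, T4 and Tn. Table 2 shows the same pattern for vaping and smoking behaviour. The text of Measures codes the prevalence items as binary.

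The notes to Table 4 give the timing: "T0: baseline, conducted approximately one week or immediately before the first core workshop" and "T2: 3 months post-intervention, after booster session, T3: 6 months post-intervention, after life skills training". Intervention and comparator says that the three program components are "conducted at three-month intervals in the course of one school year".

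The Analysis section assigns "logistic regression for [binary] susceptibility, prevalence measures, current vaping/smoking and regular vaping/smoking", adjusted for baseline intention, age, gender, parental and best friend's use, socioeconomic status, school attachment, self-esteem and distress. The child's own use at T0 is not in that list. Everything other than intention at T4 is secondary or exploratory, without multiplicity adjustment.

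**The concern.** A binary 12-month item asked 3 or 6 months after baseline counts use from before the program began. A child who tried a vape shortly before T0 and never again is positive at T2 and T3 in either arm, whatever the program did. Such children add to both arms alike, so the odds ratio moves towards 1 and the comparison becomes noisier.

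Two misreadings could follow. A null 12-month result at T2 or T3 could be taken as no early effect on use. A ratio that strengthens from T2 to T4 could be taken as a delayed effect, when part of the change comes from the window moving clear of baseline.

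**Working it through.** **Timing.** The objective counts from baseline, while the table notes say post-intervention. The two agree for this purpose: T2 follows the booster and T3 the life skills training, in a program spaced at three-month intervals that starts within about a week of T0. T2 is thus about month 3 and T3 about month 6.

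**Window before baseline.** Months before baseline = max(0, 12 − months since baseline).

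- T2: 12 − 3 = 9 months, 9/12 = 75%
- T3: 12 − 6 = 6 months, 6/12 = 50%
- T4: 12 − 12 = 0 months, 0%

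These hold to within about a week. The plan gives no expected rate or sample size for 12-month prevalence, so there is no stated figure to reproduce.

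**Effect on the contrast (illustration).** Assumptions, none from the plan: a constant monthly hazard h before baseline; k times that hazard after baseline in the control arm; a program that halves post-baseline use; and 12-month prevalence of 3% to 12% at the pre-baseline rate. The upper end is close to the 11.96% lifetime figure in the slightly older feasibility sample.

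With T months since baseline:

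- control prevalence = 1 − exp(−h(12 − T) − hkT)
- intervention prevalence = 1 − exp(−h(12 − T) − 0.5hkT)
- h = −ln(1 − p)/12

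For p = 6% and k = 1, h = 0.00516:

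| Wave | Control | Intervention | Prevalence ratio | Odds ratio |
|---|---|---|---|---|
| T2 | 0.0600 | 1 − exp(−10.5h) = 0.0527 | 0.88 | (0.0527/0.9473)/(0.06/0.94) = 0.87 |
| T3 | 0.0600 | 1 − exp(−9h) = 0.0453 | 0.76 | (0.0453/0.9547)/(0.06/0.94) = 0.74 |
| T4 | 0.0600 | 1 − exp(−6h) = 0.0305 | 0.51 | (0.0305/0.9695)/(0.06/0.94) = 0.49 |

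The linear approximation agrees: 0.75 + 0.25 × 0.5 = 0.875 at T2 and 0.50 + 0.50 × 0.5 = 0.75 at T3.

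**Range.** Over p = 3% to 12%, the prevalence ratio for the same true halving, and the share of control positives already fixed by pre-baseline use, are:

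| Post-baseline use | Ratio T2 | Ratio T3 | Fixed share T2 | Fixed share T3 |
|---|---|---|---|---|
| No rise (k = 1) | 0.88 | 0.75–0.76 | 75–76% | 50–52% |
| Doubles (k = 2) | 0.80–0.81 | 0.67–0.69 | 60–62% | 34–36% |
| Triples (k = 3) | 0.75–0.77 | 0.63–0.65 | 51–52% | 26–27% |

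Repeat use works the other way. If use does not rise and half of the possible overlap are users in both periods, the fixed share is 9/(9 + 3 − 1.5) = 86% at T2 and 6/(6 + 6 − 3) = 67% at T3.

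**Power.** Take p = 6%, k = 1 at T2 and compare with a hypothetical item covering only the time since baseline. That item would have 1 − exp(−3h) = 0.0153 against 1 − exp(−1.5h) = 0.0077.

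- Standardised difference, 12-month item: 0.0073/√(0.0600 × 0.9400 + 0.0527 × 0.9473) = 0.0224
- Standardised difference, since-baseline item: 0.0076/√(0.0153 × 0.9847 + 0.0077 × 0.9923) = 0.0507

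The ratio is 0.44. The same calculation at T3 gives 0.65. A common sample size and design effect cancel from these ratios.

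**The case against.** - **No single sentence orders this comparison.** Table 4 is a collection schedule, the hypotheses name no wave for 12-month prevalence, and the Analysis section gives models by type of outcome. Further detail is referred to the preregistration, which is not at hand. This stands: the T2 and T3 comparison is inferred from the objective, the table and the Analysis section together, and nothing in the article limits the item to T4.
- **Window months are not users.** Grade 5 was chosen to reach children before experimentation becomes more common, so use may well rise after baseline, and dilution would then be smaller. This stands, and is why a range is shown. A reader might infer that the contrasts at both waves mostly count earlier use. The documents do not support that at T3, where the window splits evenly and the share of users is unknown.
- **This is not bias in the usual sense.** Randomisation balances earlier use in expectation, and with one period of use per child the absolute risk difference is almost unchanged (0.0073 against 0.0076 above). A reader might infer that chance imbalance in earlier use would pass for a program effect. Chance imbalance adds noise but does not systematically favour either arm. The planned logistic model nevertheless yields an odds ratio, which is attenuated, and the extra positives cost power.
- **Repeating the same items at each wave is normal panel practice.** It also serves the longitudinal models that the plan mentions. This stands, and the item should stay in the questionnaires.
- **Better measures sit beside it.** The 30-day items at T2 and T3 look back only to post-baseline time. This limits the harm and supplies the remedy.

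**Conclusion.** The point holds as a minor one. On the most natural reading of the article, 12-month prevalence is contrasted between arms at two waves where about 75% (T2) and 50% (T3) of its look-back precedes baseline, in a model whose listed covariates do not separate old from new use. The window shares follow directly from the schedule. The attenuation is illustrative: a true halving of post-baseline use would show as a prevalence ratio of about 0.88 at T2 and 0.75 at T3 at constant incidence, with less dilution if use rises after baseline and more if the same children use repeatedly.

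The confirmatory analysis (intention at T4) is untouched, as is 12-month prevalence at T4. Lifetime prevalence, in the same table row, also counts pre-baseline use, and does so at every wave including T4; any text added on this point should mention it.

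**What to change.** Add a sentence to the Analysis section stating that 12-month prevalence is compared between arms at T4 only, that 30-day prevalence carries the prevalence contrasts at T2 and T3, and that 12-month prevalence at those waves is reported descriptively.

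If a comparison at T2 or T3 is still wanted, adjust for the child's own use at T0 or restrict it to baseline non-users. Both are possible with data already collected: a child negative on the 12-month item at T0 and positive at T2 must, recall error aside, have used after baseline. Keep the item in all questionnaires, since the trial is running and dropping it would break comparability across waves.

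The cost is one fewer exploratory contrast at two time points. Thirty-day use will also be rarer than 12-month use, so the gain at T2 and T3 is mainly a contrast that means what it says; it should not be expected to be well powered.

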### Trial design

A cluster-randomized, controlled, parallel-group, superiority trial will be conducted to investigate the impact of the intervention arm in comparison to an active control arm (standard curriculum taught by the school staff). Intervention lessons and outcome assessments in school will be conducted throughout the school years 2023/24, 2024/25 and 2025/26 in primary schools in Berlin, Germany, that serve Grades 5 and 6 (see Table 2 for the SPIRIT flow diagram schedule of enrolment of schools, interventions, and assessments; see Fig. 2 for the anticipated participant flow). In the German state of Berlin, primary education generally includes Grades 1–6, whereas in most other German states it typically includes Grades 1–4.

**Table 2 Tab2:** Schedule of enrolment, interventions, and assessments.

Timepoint	Study period								
	Enrolment	Allocation	Post-allocation						Close-out
	-t1	0	t0	t1^b^	t2	t3	t4	tn	tn
Enrolment:									
Eligibility screen	X								
Informed consent	X								
Allocation		X							
Interventions:									
Prevention program									
Standard curriculum (active control)									
Assessments:									
Outcomes: intention, susceptibility			X	X	X	X	X	X	X
Outcomes: vaping and smoking behavior			X		X	X	X	X	X
Proposed mechanisms / mediators^a^			X	X	X	X	X	X	X
Program evaluation: students and teachers^b^				X	X	X^c^			
Baseline covariates			X						

T0: Baseline, approximately one week or immediately before the first core workshop, T1: immediately after core workshops 1 and 2, T2: 3 months post-intervention, T3: 6 months post-intervention, T4: 12 months post-intervention, Tn = optional follow-up surveys up to the age of 21. ^a^The following measures are only assessed at T4–T^n^: Affective experience and anxiety (intervention group only), stress and problem coping self-efficacy/planning (intervention and control group). ^b^ measured only in the intervention arm. ^c^  measured in students only.

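### The primary endpoint T4 is labelled 12 months post-intervention, but on the protocol's own schedule it falls about 6 months after the last programme session

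*Protocol article*

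**What the plan says.** The protocol article gives two time origins for the same waves.

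- **Objective** (Cluster-randomized controlled trial protocol): effects are assessed "at 3, 6, and 12 months after baseline, compared to an active control group receiving the standard curriculum".
- **Primary endpoint** (Measures): the difference in intention "between intervention and control groups (primary endpoint measured at T4, 12 months post-intervention".
- **Notes to Table 2** (Trial design): "T2: 3 months post-intervention, T3: 6 months post-intervention, T4: 12 months post-intervention".
- **Notes to Table 4** (Measures): "T2: 3 months post-intervention, after booster session, T3: 6 months post-intervention, after life skills training, T4: 12 months post-intervention (assessment only".
- **Analysis**: T4 is called the 12-month follow-up, with no origin named.

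On delivery, Intervention and comparator says the programme has "three basic components that are conducted at three-month intervals in the course of one school year": the core workshop, the booster and the life skills training. Baseline is taken "approximately one week or immediately before the first core workshop", so baseline and the start of the programme fall at practically the same date. T1 is the one wave whose timing is described as immediate for all its measures: "T1: immediately after core workshops 1 and 2".

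**The concern.** T4 carries the only confirmatory test, so its time point should have one meaning. As written, a reader of the objective expects a result one year after the programme starts, and a reader of the endpoint definition expects a result one year after it ends. If the endpoint's wording is carried into the report, a positive finding will be presented as an effect that lasted 12 months without further contact, which this design does not measure.

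The label also affects the other waves and outcomes. T2 and T3 would be read as follow-ups 3 and 6 months after the programme, although a session of the programme has been delivered at each. The 12-month prevalence reported at T4 would be read as use after the programme, although on the baseline count its recall window runs over months 0 to 12 and so includes the whole delivery period.

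**Working it through.** **Inputs.** Three components at three-month intervals (Intervention and comparator). Baseline at most about a week before the first core workshop, T2 after the booster and T3 after the life skills training (notes to Table 4). Wave offsets of 3, 6 and 12 months (all sources). Taking the core workshop as month 0, the booster is at about month 3 and the life skills training, the last session, at about month 6.

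**Step 1: apply each time origin.** Wave month = origin + offset. Time since the last session = wave month − 6.

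| Wave | Origin = baseline/core workshop (0) | Since last session | Origin = end of last session (6) | Since last session |
|---|---|---|---|---|
| T2 | 0 + 3 = 3 | 3 − 6 = −3 | 6 + 3 = 9 | 9 − 6 = 3 |
| T3 | 0 + 6 = 6 | 6 − 6 = 0 | 6 + 6 = 12 | 12 − 6 = 6 |
| T4 | 0 + 12 = 12 | 12 − 6 = 6 | 6 + 12 = 18 | 18 − 6 = 12 |

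**Step 2: see which origin fits the rest of the text.**

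- Counting from baseline, T2 coincides with the booster (month 3) and T3 with the life skills training (month 6), as the notes to Table 4 require. T4 is at month 12, as the objective requires. The Data collection section also describes T0 to T4 as running from baseline to the 12-month follow-up.
- Counting from the end of the programme, T2 would be at month 9, about 6 months after the booster it is tied to, and T4 at month 18, against the objective.

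Only the baseline origin fits. On it, the interval from the last session to T4 is 12 − 6 = 6 months, and the label overstates it by 12 − 6 = 6 months, a factor of 12/6 = 2.

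**Step 3: check whether the sample size depends on this.** The plan's figure is 10 schools per arm (1,200 students), raised to 1,500. With d = 0.2, 80% power and α = 5% (two-sided assumed), a two-group comparison needs 393 per arm. The design effect is 1 + (60 − 1) × 0.005 = 1.295, so 393 × 1.295 = 508.9 per arm, and 508.9/60 = 8.48 schools, or 9 with normal quantiles. With t quantiles on 2(k − 1) degrees of freedom, power is 0.774 for k = 9 and 0.821 for k = 10. That gives 10 per arm, 2 × 10 × 60 = 1,200 students, and 1,200/0.80 = 1,500. The plan's figure is reproduced, and the calculation contains no time term. It is the same under either label.

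**The case against.** The best defence is that *intervention* in the wave labels means the core workshop. The labels are then correct, the field schedule is not in doubt, and only a word is loose. Part of this stands: the schedule can be recovered, and it is the label that is at fault. But the text does not use the word that way. The objective describes a programme of three sessions, and Intervention and comparator lists the booster and the life skills training as basic components of it. A reader who takes the endpoint definition at its word gets the wrong interval.

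It is also fair to say that the confirmatory comparison is sound. T4 involves no session in either arm, and the contrasts at T2 and T3 are declared secondary or exploratory.

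Three stronger readings are tempting, and the document does not support them.

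- *T2 and T3 are same-day readings after a session.* The notes to Table 4 say only that these waves come after the session. The phrase "assessments conducted both immediately before and after the workshop in the treatment condition (T3" belongs to the one Table 4 row marked XX, for coping, affect and anxiety. Intention, susceptibility, use and the other mediators carry a single mark at T3, and nothing comparable is said of T2. That row is itself unsettled, because a note to Table 2 places those measures only from T4 on. Same-visit measurement is plausible, since students rate their satisfaction at these waves, but it is an inference.
- *T4 may be at month 18 and run into Grade 7.* The objective and the Data collection section rule out month 18. Moreover, all three components fall within one school year, Grade 5, so even 12 months after the last session would reach no further than the end of Grade 6.
- *The items at T2 and T3 should be moved ahead of the session.* This would remedy a timing that is not established. With baseline collection already under way, it would also give early and late schools different measurement points under one label.

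**Conclusion.** The point holds as an error in the stated timing of the sole confirmatory endpoint. On the only schedule consistent with the text, T4 is about 12 months after baseline and about 6 months, not 12, after the last session. T2 falls about 3 months before the programme ends and T3 at about its end. At both waves the intervention arm has had a session beforehand, at an interval that is not stated, while control classes have had no programme session.

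This rests on taking the three-month spacing at face value, with the first component at about the date of baseline; actual school dates will vary around it. The T4 test, the covariates, the sample size and the power are unaffected, and the randomised comparison remains valid. What must change is the claim attached to the result: an effect one year after the start of the programme, about half a year after its last session.

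**What to change.** 1. Use one origin, months after T0 or the first core workshop, in the objective, the notes to Tables 2 and 4, the primary endpoint definition and the Analysis section.
2. State next to the endpoint definition that T4 is about 6 months after the last programme session.
3. Drop the description of T4 as 12 months post-intervention from the endpoint and from any conclusion drawn from it.
4. Report T2 as an assessment during delivery and T3 as one at about the end of delivery, each taken after a session in the intervention arm, and give the interval if it is known.

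The cost is wording in these places, plus an update of the registrations if they carry the same label (they were not available here). No visit, questionnaire, analysis model or sample size changes.
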